### Qualitative analysis

Interview transcripts will be analysed using thematic analysis [30]. After familiarisation of data, we will generate preliminary codes to label data of interest based on the research objectives. We will retrieve coded data to generate themes and produce summaries of interviewees’ talk on each theme, for each individual participant, and visually arrange it in a table to build an overall picture of the whole data set. This will allow for comparison across parents/carers, staff, and sites to identify variation and similarities in the final stage of interpretation of data. The next stage will involve the research team using the summaries to examine the quality and boundaries of themes identified. From this, we will finalise a thematic map refining the specifics of each theme to capture key concepts and produce analytical commentary and interpretation of the data set as a whole and connect with the original research objectives. The qualitative software package, NVivo (2015), will be used to manage the data. A proportion of transcripts will be double-coded until consensus is reached (likely to be 10%).

We will use the qualitative data to explore the perspectives of parents/carers and staff and to explore acceptability of delivering the intervention (staff) and to identify barriers and facilitators (practical, management, organisational) to implementing virtual or hybrid WMP in other sites which do not routinely use a virtual delivery.

### Economic evaluation

We will assess the costs of delivering facilitated WMP and report a cost per child of delivering WMP, including training cost and time spent on different components of the intervention.

The feasibility of collecting service use data and health-related quality-of-life (HRQL) information will also be evaluated for use in a future cost-effectiveness analysis. Service use will be collected using a modified version of the Child and Adolescent Service Use Schedule (CA-SUS) at baseline and 3 months after the intervention. We will report information on levels of service use and completeness to assess the feasibility of using the questionnaire and whether any changes should be made for a future study. We will report the mean total cost of service use per child. We will collect the self-reported EQ-5D-5L from parents/carers to assess their HRQL at baseline and 3 months after the intervention. We will calculate index values of the UK value set [31] and calculate quality-adjusted life years (QALYs) using area under the curve approach. We will report completeness, mean index value at each timepoint, and QALYs over the course of the study.

### Oversight and monitoring

A Study Management Group (SMG) will include the chief investigators, co-applicants, collaborators, trial manager, data manager, health economist, statistician, and administrator. The SMG will meet approximately every 4–6 weeks throughout the course of the study. Members will be required to sign up to the remit and conditions as set out in the SMG Charter.

An Executive Committee (EC) has been set up to provide independent oversight. It comprises of an independent chair, one local PI responsible for a (likely) participating site (who brings experience of WMP implementation and study participation), one independent WMP expert (research in families and children), and one member of the Parent Carer Advisory Group. The EC will meet at least three times during the course of the study to provide overall supervision for the trial and provide advice through its independent chair. EC members will be required to sign up to the remit and conditions as set out in the EC Charter. Given the low-risk nature of the trial, we will ask the EC to act as Data Monitoring Committee (DMC).

### Adverse event reporting and harms

All SAEs must be reported immediately (and within 24 h of knowledge of the event) by the principal investigator at the participating site to the study team unless the SAE is specified as not requiring immediate reporting. In addition, for the purposes of this study, the removal of a child from the biological family (or unplanned removal more specifically) is considered to be an adverse event, and any instances will be recorded.

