Children in care — children who are under the care of a local authority (child welfare system) — are known to be at high risk of developing mental health problems in childhood and adolescence [7–9]. Watch Me Play! (WMP) was originally developed in the context of a local authority mental health service for children in care to offer an intervention to babies and children who would otherwise be offered little. It is an early intervention designed to support caregiver attunement and attention to the child to promote child social-emotional well-being and thereby mental health resilience. WMP can be delivered in the first weeks of a baby’s life up to the age of 8 years depending on the kind of play they enjoy and are ready for. WMP involves a parent or carer watching the child play freely, while the parent talks with their child about their play for a period of up to 20 min (this is called one session). The parents prepare by switching off the TV, phone, and screens and putting out a small selection of nonelectronic toys. The parent watches their child as they play, only joining in if the child invites them to do so, allowing the child to lead the play, as long as this is safe. The parent follows the child’s play and describes what the child is doing. The same ideas apply in WMP with babies before they are of an age to play with toys: the parent notices and follows the baby’s signals; mirrors facial expressions, movements, and sounds; and talks to the baby, imitating the baby’s expressions or sounds as if having a conversation. This can give an idea of what the baby is interested in. The parent does not direct the child’s play. The parent does not engage in other activities, giving instead their full attention to the child or baby during the 5- to 20-min session. The parents are encouraged to record their reflections in a diary at the end of a session. Some sessions are facilitated by a trained practitioner who joins the parent in watching the child or baby, either in person or online (using secure video conferencing software), talking to the child about their play, and providing prompts to the parent where necessary. Towards the end of the session, the trained practitioner discusses the child’s play with the parent: what they saw, what was new or not new, and what the child enjoyed or was frustrated by and about the parent’s experience: what they noticed, enjoyed, or found difficult. A facilitated session with a practitioner lasts up to 1 h. WMP is a flexible model that fits in with parents’ time availability, the needs of the family, and the resources that services can offer.

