### Study design and setting

A non-randomised single group feasibility study, including a process evaluation. Participants will be recruited from early years, children’s health services and some social care, education, or voluntary services. These are services designed to support families of young children. The study will be carried out at sites spread across the UK serving a mix of populations. Sites may include a mixture of CAMHS, child development teams, foster care services, and mental health services for children in care. We will offer to train up to three members of staff in WMP so that each service has at least three staff trained. We will aim to recruit some sites with no prior exposure to WMP so we can investigate the feasibility of rolling out training.

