### Inclusion criteria

Parents or carers of children aged 0 to 8 years old who have a referral to or have been accepted by an early years/children’s service within the United Kingdom (UK). Parents must be able to complete outcome measures in English (with support if required, whereby a researcher can talk through the questionnaire via telephone). Parents/carers of children with any type of mental health problem, and/or developmental delay, will not be excluded from taking part provided all eligibility criteria are met.

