### Sample size

The study aims to recruit up to 40 families (1 caregiver of 1 child) from across up to 15 sites. As this is a feasibility study, a power calculation was not utilised to estimate the target sample size. Instead, we looked to the literature to guide us in deciding an appropriate recruitment target.

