### Recruitment

Participants will be identified by services as potentially eligible: we will ask the direct care team to identify children within the right age range and in particular those with a social worker either currently or in the past 24 months. Members of the direct care team will email parents/carers a brief information leaflet (briefing sheet) about the study. Parents interested in taking part or knowing more will either go straight to the screening/consent questionnaire via a link code on the briefing sheet or contact the research team via contact details on the briefing sheet. The researcher will discuss the study in more detail with the participants. The screening/consent questionnaire will contain the full participant information sheet. Those who provide informed consent will be screened for eligibility. We will proactively recruit parents/carers of children with or who have had a social worker, noting barriers and facilitators to recruitment where they exist. Recruitment will be monitored to ensure diversity in relation to ethnicity, low SES, and poor literacy, as per NIHR INCLUDE and INCLUDE ethnicity guidance [27, 28]. We will encourage BME participation following guidance from the Centre for BME health (https://centreforbmehealth.org.uk/).

A £50 voucher at baseline and follow-up will be offered to families taking part. A £50 voucher will also be offered to participants taking part in qualitative interviews and those who take part in the free play video recording. To address digital poverty and support the inclusion of those who might struggle to participate, we will offer £20 to support those who may not have adequate Internet data to undertake the online evaluation.

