### Data collection

Outcomes will be measured at baseline and post intervention. All outcomes, except for parent–child interaction, will be measured through parent report (questionnaires to be completed via a survey link). Parent–child interaction during free play will be video recorded (for 20 min) by researchers remotely during baseline only for a smaller number of randomly selected participants, from those who have consented to be contacted (up to *n* = 8). The purpose is to assess the feasibility and acceptability of collecting data in this way in a future trial. Additional information will be collected at screening only on the presence of developmental delay and on the child’s status as in contact with social worker.

In the event that participants’ follow-up data collection appointments are missed at the proposed time points, the research team will contact the participant by telephone to rearrange the appointment as soon as possible. Follow-up assessments for all participants will be conducted 3 months from baseline with a + / − 2-week window.

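### The one study-specific harm event, removal from the biological family, does not fit children already placed outside that family, and it is unclear whether planned removals count

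*Protocol article*

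**What the plan says.** All references are to the protocol article.

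- **Adverse event reporting and harms** has two parts. The first is general: "All SAEs must be reported immediately (and within 24 h of knowledge of the event"), with an exemption for SAEs specified elsewhere as not needing immediate reporting. The second is specific to this study: "the removal of a child from the biological family (or unplanned removal more specifically) is considered to be an adverse event". Any instance is to be recorded.
- **Inclusion criteria** admit carers as well as parents: "Parents or carers of children aged 0 to 8 years old who have a referral to or have been accepted by an early years/children’s service". Neither the inclusion nor the exclusion criteria rule out children in care.
- **Study design and setting** lists possible sites: "Sites may include a mixture of CAMHS, child development teams, foster care services, and mental health services for children in care".
- **Recruitment** gives the active target: "We will proactively recruit parents/carers of children with or who have had a social worker".
- **Background** says that WMP was first developed in a local authority mental health service for children in care. It describes such children as being under local authority care and says that they "are known to be at high risk of developing mental health problems in childhood and adolescence".
- **Data collection** names the additional status items: "Additional information will be collected at screening only on the presence of developmental delay and on the child’s status as in contact with social worker".
- The section on **Sample size** sets an upper limit on both families and services: "The study aims to recruit up to 40 families (1 caregiver of 1 child) from across up to 15 sites".

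**The concern.** A harm event should be able to occur in everyone whose safety it is meant to describe. This one assumes that the child lives with the biological family at entry. For a child who does not, the comparable adverse turn is an unplanned end of the current placement, and the definition does not reach it.

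Three things are at stake:

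- **Interpretation of a zero.** Among placed children a count of zero would arise from the definition itself and would say nothing about safety.
- **Consistency between sites.** The sentence offers a broad rule (any removal) and a narrow one (unplanned removal only) without choosing.
- **The 3-month data.** Every outcome except the baseline play video is reported by the parent or carer. If the placement changes, the respondent may change or be lost. That bears on retention and on the planned classification of CBCL change from baseline.

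The Discussion describes this as the first evaluation of WMP, meant to inform whether further evaluation is appropriate. A definition used here may well be carried forward.

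**Working it through.** The article states no figure on this point, so there is none to reproduce. The check sets the passages side by side.

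**1. Who can enter?** A carer of a child aged 0 to 8 who is referred to, or accepted by, an early years or children's service. A foster, kinship or adoptive carer meets that description. The list of possible sites makes the entry of foster carers a foreseen possibility.

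**2. Can the named event happen to each child?**

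| Child's situation at entry | Removal from biological family possible? | Equivalent event named in the article? |
|---|---|---|
| Living with biological family | Yes | Not needed |
| Under local authority care but living with biological family | Yes | Not needed |
| In a foster, kinship or adoptive placement outside the biological family | Generally no | No |

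The definition therefore fails in the third row only.

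**3. Could the children at risk be counted afterwards?** The care-related item named is social worker contact. That is wider than being in care, and it does not say where the child lives. Demographic information is also collected at baseline, but the article does not list its contents. On what is shown, the number of children at risk of the named event cannot be derived.

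**4. Does a planned removal count?** Under the words before the parenthesis, yes. Under the words inside it, no. The same planned removal could be recorded at one site and not at another, with up to 15 sites involved. This needs no assumption about case mix.

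**5. How many children are affected?** If a share *p* of the 40 families care for a child placed outside the biological family, the number is 40 × *p*. The article gives no *p*. Purely as an assumption, *p* = 0.10 gives 40 × 0.10 = 4 children, and *p* = 0.40 gives 40 × 0.40 = 16. If no foster or in-care service joins, the number could be close to zero.

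**The case against.** The strongest reply is that this is a condensed article. It is drafted from protocol Version 4.0, which is not at hand, and adverse event definitions and event lists usually sit in the full document. The removal event is an addition to a general SAE stream, the modified CA-SUS also asks about services, and the study is described as low risk with no formal tests and no progression criteria. The parenthesis might also be read as narrowing the event to unplanned removal.

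Much of this stands, and it rules out several stronger readings that a reader might infer:

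- *That placement breakdown will go unrecorded.* The article only fails to name it. SAE reporting, the CA-SUS, interviews or the full protocol might capture it, though none is shown to do so systematically.
- *That the study sets out to recruit children in care.* The site list is permissive, and the active target is social worker contact.
- *That the event is impossible for every child in care.* The article does not say that all such children live apart from their biological family.
- *That these are the highest-risk children.* The article says high risk and gives no ranking.
- *That a harm rate will be understated.* No removal rate is planned, only recording of instances, so a contrast of percentages would need invented inputs for an analysis the article does not describe.
- *That such events will be hidden in attrition.* Retention is counted and examined in the process evaluation, and missed follow-ups prompt a telephone call.

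What the reply does not remove is the mismatch itself. The article does not leave this event to another document. It states the definition, and the stated definition does not fit the stated population. If the parenthesis is meant to narrow the event, the sentence should say so outright.

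**Conclusion.** The concern holds in a limited form. The study-specific event generally cannot occur for children already placed outside the biological family. Eligibility and the possible site types allow such children in, and no equivalent event is named for them. Separately, the sentence does not settle whether planned removals count.

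The conclusion rests on the article's wording alone, plus the assumption that at least some placed children are enrolled; the planned-removal point does not need that assumption. The number affected is unknown. This is an inexpensive improvement to harm capture. It does not undermine the feasibility design, and no stated decision turns on the count.

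**What to change.** Replace the sentence under Adverse event reporting and harms with one recorded event: *any unplanned change of the child's main placement or caregiver during the study, including removal from the biological family and unplanned ending of a foster, kinship or adoptive placement*. Record planned moves separately, so that they are neither lost nor mixed with the event.

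Two data items support this:

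- Placement type at baseline, if the demographic form does not already hold it, so that each count can be given beside the number of children at risk.
- A flag on 3-month data where the reporting carer differs from the one at baseline.

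Plain counts are enough; no subgroup analysis is needed in at most 40 families. The cost is one reworded sentence, one or two form items and possibly a few more reports from sites. If the full protocol already covers placement breakdown, aligning the wording is all that remains.

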### Data protection

Data will be stored confidentially on secure password-protected severs and accordance with the Data Protection Act 2018 and General Data Protection Regulation (GDPR). Personal information will be collected, kept, and stored securely in compliance with UK GDPR. The research team and staff at participating sites are trained in GDPR compliance. The data controller is the Tavistock and Portman NHS Foundation Trust. The data custodian for this study is the CI, [name]. A Data Protection Impact Assessment (DPIA) has been completed as part of an overall trial risk assessment.

## Discussion

The proposed feasibility study will address feasibility and acceptability questions associated with delivery of Watch Me Play! for families referred to early years and children’s services, either currently experiencing mental health problems or at significant risk of developing mental health problems in later life. This is the first evaluation of WMP and the first evaluation with this population. Results of this study will indicate whether it is appropriate to conduct further evaluations of WMP, including whether a randomised feasibility evaluation with formal progression criteria is warranted.

### Study status

This manuscript has been drafted according to Version 4.0 (11th January 2024) of the trial protocol. The final report will follow the CONSORT (Consolidated Standards of Reporting Trials) statement. The study is sponsored by the Tavistock and Portman NHS Foundation Trust ([contact]).

## Data Availability

The datasets used and/or analysed during the current study are available from the corresponding author on reasonable request.

## Abbreviations

CTR: Centre for Trials Research
CI: Chief investigator
GDPR: General Data Protection Regulation
UK: United Kingdom
DMC: Data Monitoring Committee
MRC: Medical Research Council
RCT: Randomised controlled trial
DPIA: Data Protection Impact Assessment
SAE: Serious adverse event
SMG: Study Management Group
EC: Executive Committee
WMP: Watch Me Play!
CONSORT: Consolidated Standards of Reporting Trials
